# Effectiveness of three treatment strategies on occupational limitations and quality of life for patients with non-specific chronic low back pain: Is a multidisciplinary approach the key feature to success: study protocol for a randomized controlled trial

**DOI:** 10.1186/1471-2474-15-131

**Published:** 2014-04-16

**Keywords:** Chronic non-specific low back pain, Multidisciplinary rehabilitation, Private physiotherapy, Mixed strategies

## Abstract

**Background:**

Chronic low back pain (cLBP) is a significant public health problem, being the primary cause of work absenteeism, as well as affecting sufferers’ quality of life, in industrialized society. International guidelines recommend intensive multidisciplinary approaches for patients with cLBP. However, these costly and time-consuming programs can only be offered to a minority of the most heavily affected patients and therefore do not seem likely to respond to public health requirements. Lighter programs may be an alternative to full time hospital-based programs with valuable results in terms of disability and occupational activity for cLBP patients. It is therefore important to define both what the determining components of management to improve activity restriction are and how to treat a larger number of patients more effectively at a lower cost. The aim of this study is to compare three programs with various levels of intensity and multidisciplinary.

**Methods/Design:**

This paper describes the protocol for a prospective, randomized, controlled, clinical trial in working aged patients with cLBP. Three treatment strategies are compared: (1) intensive and multidisciplinary program conducted in a rehabilitation center; (2) less intensive outpatient program conducted by a private physiotherapist; (3) mixed strategy combining the same out program with a multidisciplinary intervention. The primary outcome of the trial is the impact of the mixed strategy on being able to work compared to hospital centered-program and out program. The secondary outcome is the impact of the mixed strategy on quality of life and social ability compared to the two others programs. The intervention part of the trial programs will take 5 weeks and observational follow-up will take 12 months. The sample size will be 180 participants (60 for each arm). The project has been approved by the Ethical Committee of Angers Hospital, France.

**Discussion:**

On the hypothesis that a multidisciplinary approach is the key feature to programs success in reducing social and occupational impairment in cLBP patients, we suggest that it is possible to achieve the same results with less intensive strategies if a multidisciplinary approach is maintained.

**Trial registration:**

Current Controlled Trials NCT02030171.

## Background

Chronic low back pain (cLBP) is a significant public health problem, being an important cause of work absenteeism, as well as affecting sufferers’ quality of life [1,2]. LBP remains the primary cause of absenteeism and disability in every industrialized society and patients who develop cLBP (pain and disability persisting for more than 12 consecutive weeks) use more than 80% of all health resources for back pain [3].

International Guidelines recommend the use of supervised active exercises, multidisciplinary approaches, cognitive-behavioral therapies and measures of social and professional order for patients with cLBP [1,4,5]. Referral for these programs is preferred for patients with cLBP on prolonged sick leave [1,5,6] and treatment management is increasingly focused on the prevention of activity improvement and ability restrictions, and have as an explicit goal return to or staying at work, regardless of changes in the painful condition. The impact of functional recovery has been assessed in terms of pain, disability and occupation [7-17]. Although pain outcomes differ between studies, action to improve functional and occupational capacity are consistently encouraging, particularly in France [11,14,16-18]. However, these costly and time-consuming intensive multidisciplinary programs can only be offered to a minority of the most heavily affected patients and therefore do not seem likely to respond to public health requirements.

Lighter programs may be an alternative to full time hospital-based programs at the same stage of treatment strategy with valuable results in terms of disability and occupational activity for cLBP patients [16,17,19-22]. It is therefore important to define both what the determining components of management to improve activity restriction are, including occupational status, and how to include more hospital-independent programs in our health care system to treat a larger number of patients more effectively at a lower cost.

This study follows two previous studies by our team:

- The first [16,23] prospectively evaluated an intensive multidisciplinary Functional Restoration Program (FRP). A cohort of 87 patients had been treated and followed up two years after treatment and the results revealed a significant reduction (60%) in the number of days’ sick leave during the two years following inclusion.

- The second [22] randomly compared the same FRP to less intensive Ambulatory-based Individual Physiotherapy (AIP): 64 patients were included in the FRP arm and 68 patients in the AIP arm. This study demonstrated the superiority of the first program in terms of number of days’ sick leave during the 6 months following treatment. The difference was also highly significant with regard to outcomes assessing physical capacity, but there was no between-arm difference for pain intensity or quality of life criteria. The hypothesis proposed to explain this result was that the crucial difference between the two programs was the multidisciplinary nature of the approach, and we considered that it would be possible to achieve the same results with less intensive AIP if this multidisciplinary approach was maintained. Obtaining such information would potentially allow a significant increase in the number of patients offered a multidisciplinary strategy by increasing treatment availability and decreasing program costs.

### Aim of the study

On the hypothesis that a multidisciplinary approach is the key feature to FRP success in reducing social and occupational impairment in cLBP patients, we suggest that it is possible to achieve the same results with less intensive AIP strategies than FRP if a multidisciplinary approach is maintained. The aim of this study was to compare three treatment strategies to demonstrate this hypothesis:

- Intensive and multidisciplinary FRP conducted in a rehabilitation center;

- Less intensive outpatient AIP conducted by a private physiotherapist member of a care network;

- Mixed strategy combining the same AIP with multidisciplinary intervention.

### Hypothesis regarding the primary aims

The expected benefits for subjects participating in the study are improvement in their quality of life and improved remaining at work, resulting in a decrease in the number of days’ sick leave, and reducing the risk of progressive exclusion from work.

The main results expected from the study are (1) a significant difference between the mixed strategy and AIP in the number of days’ sick leave and quality of life and (2) no significant difference in these criteria between FRP and the mixed strategy despite any difference in outcomes evaluating only impairments and activity limitations. Such results would show that a multidisciplinary approach is the key feature to the success of such programs.

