### Analyses

#### Sample size

Based on the available literature [7-15] and following previous trials [16,17,22], we assume that a difference of 30 days’ sick leave a year between treatment arms is clinically significant. With a sample size of 60 patients in each treatment arm, accepting an alpha error of 0.05 and a power of 0.80, it is possible to measure a minimum difference of 30 days’ sick leave during the subsequent 12 months’ treatment. To compensate for an estimated 10% dropout rate, a total of 180 people will be included.

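### The claim that the mixed strategy matches FRP rests on a non-significant test of difference, with no margin or confidence-interval rule

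*Protocol article*

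**What the plan says.** The Aim of the study section frames the mixed-versus-FRP question as one of sameness: "we suggest that it is possible to achieve the same results with less intensive AIP strategies than FRP", provided that the multidisciplinary element is kept. The abstract's Discussion says the same: "we suggest that it is possible to achieve the same results with less intensive strategies if a multidisciplinary approach is maintained".

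Hypothesis regarding the primary aims then names two main expected results, each covering sick leave and quality of life. The first is a significant difference between the mixed strategy and AIP. The second is "no significant difference in these criteria between FRP and the mixed strategy". The section closes: "Such results would show that a multidisciplinary approach is the key feature to the success of such programs".

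Analyses of efficacy gives Student's test as the between-group comparison for quantitative data, at a significance level of 0.05. Sample size assumes that "a difference of 30 days’ sick leave a year between treatment arms is clinically significant" and states, "accepting an alpha error of 0.05 and a power of 0.80", that with 60 patients per arm "it is possible to measure a minimum difference of 30 days’ sick leave during the subsequent 12 months’ treatment". The 30 days serves only as a difference to detect. It is never used as a margin.

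**The concern.** Student's test asks whether two arms differ. A p-value above 0.05 says only that the data did not exclude a zero difference. They may equally fail to exclude a large one. The protocol nonetheless assigns a meaning to that null result in advance: with a positive mixed-versus-AIP result, it is taken to show that the lighter programme does what FRP does.

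The Discussion section links this conclusion to modified ambulatory programmes for large populations. If the mixed strategy were materially worse than FRP on sick leave, the planned reading could still present the two as alike. The protocol sets no limit on how large a loss could pass in this way.

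**Working it through.** **Inputs.** From Sample size: difference 30 days, alpha 0.05, power 0.80, 60 per arm, 10% dropout (60 × 0.9 = 54 per arm). From Analyses of efficacy: Student's test. Not stated, so assumed: a two-sided test, and the SD of sick-leave days.

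**Step 1: the protocol's own figure.** The sample size cannot be run forward without an SD, so it is solved for one. In a two-sided t-test with power 0.80, the detectable standardised difference is 0.5157 at 60 per arm and 0.5441 at 54.
- 60 analysed: SD = 30 / 0.5157 = 58.2 days.
- 54 analysed: SD = 30 / 0.5441 = 55.1 days.

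The text can be read either way, since 60 per arm is given both as the powered number and as the number that allows for dropout.

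**Step 2: precision.** Standard error = SD × √(2/n).
- n = 60: 58.2 × √(2/60) = 10.6; 95% half-width = 1.98 × 10.6 ≈ 21 days.
- n = 54, same SD: 58.2 × √(2/54) = 11.2; half-width ≈ 22 days.

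An observed loss of 20 days at 60 per arm is therefore non-significant, while its interval reaches about 20 + 21 = 41 days.

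**Step 3: chance of a non-significant mixed-versus-FRP test.** This is 1 − power at each true loss (non-central t). At 30 days and n = 60, the ratio is 30 / 10.6 = 2.82, and 1 − Φ(2.82 − 1.98) ≈ 0.20.

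| True loss, mixed vs FRP | 60 per arm, SD 58.2 | 54 per arm, SD 58.2 |
|---|---|---|
| 15 days | 71% | 74% |
| 20 days | 54% | 58% |
| 30 days | 20% | 24% |
| 40 days | 4% | 6% |

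With 54 per arm and SD 55.1, the first column applies.

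**Step 4: sensitivity to the SD.** For a 30-day loss with 60 per arm: about 2% at SD 40, 47% at SD 80, 63% at SD 100.

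**Step 5: the full expected pattern on sick leave** (mixed significantly better than AIP and non-significant against FRP). This was simulated with the mixed arm shared by both tests and mixed truly 30 days better than AIP.
- Mixed 15 days worse than FRP: 62% (60 per arm), 61% (54 per arm).
- Mixed 30 days worse than FRP: 19% (60 per arm), 23% (54 per arm).

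**Step 6: a non-inferiority rule on the same data.** If the upper 95% limit must fall below 30 days, a true 30-day loss passes 2.5% of the time. Power at a true difference of 0 is the chance that the upper limit falls below the margin, roughly Φ(margin / standard error − 1.98).
- 30-day margin: 80% (60 per arm), 76% (54 per arm).
- 15-day margin: 29% (60 per arm), 26% (54 per arm).

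For 80% power by the normal approximation (SD 58.6, before dropout), a 30-day margin needs 60 per arm and a 15-day margin 240.

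**The case against.** The best defence is that the hypothesis section lists expectations, not a formal decision rule, and that the Discussion speaks only of findings that might help to confirm the hypothesis. A margin might also appear in an analysis plan that is not shown. The first part has some force. But the closing sentence of the hypothesis section states what the null result would show. The objection is to that stated inference, which an analysis plan with a margin would have to contradict.

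Four stronger readings are tempting and are not supported.
- A reader might infer that a clinically important loss would usually pass as equal. The only loss the protocol calls clinically significant is 30 days, where the figure is 20–24% at the implied SD. Rates above one half belong to losses of 20 days or less, or to an SD well above the implied value.
- A reader might infer that missing data always favour the desired conclusion. That holds for the mixed-versus-FRP test alone. The full pattern also needs a significant result against AIP, which missing data make harder to reach. With 60, 54 and 45 per arm it goes 62%, 61%, 58% at a 15-day loss, but 19%, 23%, 28% at a 30-day loss.
- A reader might infer that expecting the mixed strategy to beat AIP on quality of life contradicts the earlier trial, where "there was no between-arm difference for pain intensity or quality of life criteria" in FRP versus AIP. It does not. That null is not proof of equality, and the mixed strategy includes workplace and general-practitioner components not described for FRP.
- A reader might infer that the repair is free at any margin. It needs no more patients only near 30 days, and with that margin a true 15-day loss still passes 26–29% of the time.

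**Conclusion.** The concern stands in this form: a conclusion of sameness is tied to a non-significant test of difference, without a margin or interval rule. At the protocol's own 30-day threshold the chance of missing the loss is about 20%, or 24% with SD 58 and 54 analysed per arm. That is eight to ten times the 2.5% of a non-inferiority test with that margin. The size depends on an SD that the document does not give and on a two-sided test. The error of inference depends on neither.

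On quality of life the supportable point is limited. The earlier trial did not find a difference even between FRP and AIP, so a non-significant mixed-versus-FRP result there cannot show that the multidisciplinary element preserved an effect.

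This should be corrected before analysis, because it bears on the trial's central conclusion.

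**What to change.** Before the data are analysed:

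1. Replace the no-significant-difference criterion with a rule on the two-sided 95% confidence interval for mixed minus FRP in sick-leave days over 12 months. Claim that the mixed strategy is not materially worse only if the upper limit is below a pre-stated, justified margin no larger than 30 days. Otherwise report the comparison as inconclusive.
2. State the power from Step 6 for the chosen margin, with the assumed SD and its source.
3. Report FRP versus AIP alongside, to show whether this trial could detect FRP's advantage.
4. For quality of life, report the estimate and interval, and draw no claim of sameness from a non-significant test.

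The cost is a change to the hypothesis wording and the analysis rule. Similarity becomes harder to claim. Trial status says that data collection is ongoing, and participants and practitioners are not blinded, so the margin would be set late. Its date and justification should be recorded, and it should be fixed without reference to outcomes by arm.

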## Methods/Design

### Study design

This is a mono-center study with a prospective randomized controlled design, comparing the effectiveness of three treatment strategies. Participants with non-specific cLBP are being randomized into one of the three arms of the study, with a follow-up of 1 year (see Figure 1). The randomized controlled trial (RCT) includes both effectiveness and an economic study.

**Figure 1 F1:**
[figure not shown]
Clinical study design.

### Setting

Participants are referred to a French cLBP care network to support medical and occupational issues. This network includes a multidisciplinary cLBP clinic with a rehabilitation physician, an occupational health practitioner (OP), a psychologist and an occupational health nurse. Rehabilitation programs are provided in a rehabilitation center or by one of the private physiotherapists of the network. After attending the multidisciplinary LBP clinic and randomization, participants are subsequently referred to the rehabilitation center or to a private physiotherapist of the region or both, depending on the arm of the trial. The study is expected to last three years and will stop once completed, ie at the end of the last participant’s follow-up.

### Ethical aspects

This investigation is being conducted according to the international recommendations for cLBP management [1,4,5]. All patients are asked to provide informed written consent prior to randomization, using standard forms. Information for the participants and their agreement to study participation is considered “informed consent”. It is pointed out to the participants that study participation is voluntary and that they may refuse to participate or discontinue participation at any time without disadvantages or loss of benefits. According to the national data protection laws, all personal data are treated as confidential and used only for scientific purposes. Ethical approval has been granted by the French Ethics Committee.

### Participants

Subjects of working age suffering from non-specific cLBP diagnosed according to generally accepted scientific criteria are acceptable for enrolment [1,24].

#### Inclusion criteria

Patients may be included if they are able to sign the informed consent form, and are aged between 18 and 55 years, with non-specific LBP lasting for at least 3 months without improvement, LBP leading to at least 1 month’s sick leave during the preceding year and/or 3 months’ sick leave during the preceding two years, and an open-ended or fixed-term contract of work in the public or private sector.

#### Exclusion criteria

Patient who are unable to give informed consent, have a disability preventing them attending physical therapy with a physiotherapist of the study, with diagnosed malignant, traumatic, infectious or inflammatory LBP, acute sciatica, symptomatic lumbar spinal canal stenosis or progressive spondylolisthesis, cardiac or respiratory insufficiency (diagnosed after exercise stress test on bicycle ergometer), articular or neurologic impairment incompatible with a physical exercise program (but not uncomplicated depression), psychiatric disorders precluding participation in group therapy, pregnancy or breast-feeding, legal protection for vulnerable individuals, lack of health insurance are excluded.

#### Withdrawal criteria

A patient may leave the study at his own or an investigator’s initiative. The exclusion criteria are expected to extent to withdrawal of consent for participation, development of a criterion for non-inclusion or administration of a prohibited treatment during the 5 weeks’ course.

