### Screening for participation and randomization

Participants are selected by the study investigators from patients referred to the regional cLBP network. When a patient is referred to the regional cLBP network, the rehabilitation physician screens information provided by the referring general practitioner or medical specialist before referring him to the multidisciplinary cLBP clinic. Each patient undergoes a standardized multidisciplinary evaluation including a medical examination, psychological, social and occupational interviews and self-administered questionnaires. The rehabilitation physician verifies whether an extensive physical examination and imaging or laboratory studies according the guidelines [24] have been performed if necessary. The rehabilitation physician explains the study procedure and, if someone meets the inclusion criteria and has none of the exclusion criteria, asks the patient to sign the informed consent form. After signing, one of the three treatment strategies is randomly allocated to each patient.

The randomization procedure of participants is determined by a computer randomization feature which automatically allocates the patient to one of the treatment strategies. This system has been described in previous studies [16,17,22]. An independent research assistant prepares envelopes and numbers them sequentially according to the randomization list. Envelopes are given to the rehabilitation physician who opens them at the end of the clinical evaluations described above.

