#### Concomitant treatments

All other treatments are allowed, except for the following: physiotherapy other than AIP in the cLBP regional network, other manual techniques, surgery for back pain, and hospitalization for LBP. In the case of administration of any of these treatments, patients are eliminated from the study.

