#### Primary outcome measurement

The primary outcome of the trial is represented by the effectiveness of the impact of the mixed strategy on being able to work compared to FRP and AIP. Being fit for work is evaluated by the duration of sick leave in 1 year: the number of days’ sick leave during the preceding 12 months and during the 12 months of the study is collected for each patient and verified by checking with the health insurance provider.

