### Assessment and procedures

The accuracy and completeness of the data collected is checked weekly by an independent research assistant to provide a suitable level of quality for the study. In particular, controls review the quality and completeness of outcomes, treatment execution and monitoring modalities, the dropout rate, and correct respect of application of enrolment criteria.

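### Randomised patients are removed from the study, not only from their programme, for events that can be related to sick leave; taken literally this defeats the intention-to-treat comparison

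*Protocol article*

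**What the plan says.** All references are to the protocol article.

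- **Withdrawal criteria.** "A patient may leave the study at his own or an investigator"'s initiative. The next sentence extends the exclusion criteria to withdrawal of consent and to "development of a criterion for non-inclusion or administration of a prohibited treatment during the 5 weeks" of the course.
- **Concomitant treatments.** The prohibited treatments are physiotherapy outside the network's AIP, "other manual techniques, surgery for back pain, and hospitalization for LBP". The consequence is stated without a time limit: "In the case of administration of any of these treatments, patients are eliminated from the study".
- **Exclusion criteria.** The criteria that could develop later include "acute sciatica, symptomatic lumbar spinal canal stenosis or progressive spondylolisthesis" and impairment incompatible with exercise, as well as pregnancy, legal protection and lack of health insurance.
- **Screening for participation and randomization.** "Envelopes are given to the rehabilitation physician who opens them". The Discussion adds that practitioners cannot be blinded.
- **Primary outcome measurement.** Sick leave over 12 months is collected for each patient and "verified by checking with the health insurance provider".
- **Analyses of efficacy.** The comparison is by intention to treat. Dropouts and missing values get a post-hoc analysis, and dropouts' characteristics are compared with those of completers.

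**The concern.** Stopping a patient's programme on safety grounds is reasonable. The fault is that stopping treatment and leaving the study are one step here. Several triggers mark patients whose backs are getting worse, and these are the patients likely to have long sick leave. Removing them takes poor outcomes out of an arm. Other triggers, such as pregnancy or loss of insurance, need not be related to the outcome.

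Removal can also depend on the arm. The rehabilitation physician knows the allocation. Contact differs too: the article describes weekly attendance at a specialist clinic in FRP and a weekly day at the rehabilitation center in the mixed strategy, but nothing comparable in AIP. A trigger could therefore be noticed more often in some arms than in others. Unequal removal is possible, not shown.

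Both expected results are exposed. More outcome-related removal in the mixed arm would flatter mixed against AIP. More in FRP would flatter FRP against mixed. Every loss of patients also makes a non-significant difference between FRP and mixed easier to reach, and that is the second result the trial hopes for.

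The time limit is unclear as well. The 5-week limit under Withdrawal criteria may cover all triggers or prohibited treatment only, and Concomitant treatments gives no limit.

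**Working it through.** **Reading the sections together.** Concomitant treatments states an affirmative rule of elimination from the study. Withdrawal criteria uses the same scope, the study, and nothing in either section says that outcome data are still collected afterwards. Analyses of efficacy promises intention to treat. If the elimination rule is followed literally, randomised patients are missing from that comparison for reasons that arise after randomisation.

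**Inputs from the Sample size section.** Difference of 30 days, 60 patients per arm, alpha 0.05 (taken as two-sided), power 0.80, 10% dropout. No SD is stated, so the sample size cannot be reproduced independently; the SD has to be solved for.

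**Implied SD.** A two-sample t test with 60 per arm has 80% power at a standardised difference of d = 0.516.

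- SD = 30 / 0.516 = 58.2 days.
- The normal approximation gives 58.6 days. If only 54 per arm are analysed (60 less 10%), it gives 55.6 days.

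**Bias formula.** Let p be the fraction removed from an arm and D the excess mean sick leave of those removed over those who stay. Then:

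- mean of those who stay = arm mean − p × D
- shift in the between-arm difference = |p1 × D1 − p2 × D2|

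**Assumptions, not in the documents.** D lies between 0.5 and 1.5 SD, that is 0.5 × 58.2 = 29.1 days to 1.5 × 58.2 = 87.3 days, and the outcome of removed patients is not obtained.

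| Scenario | Shift (days) | Share of 30 days |
|---|---|---|
| Same D, gap of 1/60 | 29.1/60 to 87.3/60 = 0.5 to 1.5 | 2% to 5% |
| Same D, gap of 3/60 | 3 × 29.1/60 to 3 × 87.3/60 = 1.5 to 4.4 | 5% to 15% |
| Equal p = 3/60, D = 29.1 in one arm and 87.3 in the other | 3/60 × 58.2 = 2.9 | 10% |
| Equal p and equal D | 0 | 0% |

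A gap of 3 in 60 is half of the 10% dropout allowance (6 per arm). Equal counts alone do not protect the comparison; the shift is zero only when p × D is the same in both arms.

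**A harsher assumption.** If 15% were removed from AIP and 5% from mixed, with D of 30, 60 or 100 days, a true 30-day difference would shrink by 0.10 × D = 3, 6 or 10 days. Nothing in the article suggests so large an imbalance.

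**The case against.** The strongest reply is that leaving a study and being dropped from the analysis are different things. The article never says that collected data are discarded or that the insurer check stops. It states intention to treat without exception, so a reading exists in which everything is compatible, and a condensed article may leave the details to the full protocol. This stands in part: the conflict arises when the rule is followed literally. But elimination from the study is a stated rule, not an omitted detail, and a site following it would stop collecting data.

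Other points on that side:

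- **Dropout analysis.** The plan will compare dropouts with completers and examine missing values. This shows that the authors mean to look at these patients, but it restores no outcomes.
- **Investigator's initiative.** The sentence that follows may be the list of permitted grounds, in which case there is no free discretion. The text does not settle this. The other two triggers are enough for the concern.
- **Five-week window.** If the limit governs every trigger, few patients may have surgery or be hospitalised in that time. This lowers the likely size, but an early removal can still cost the 12-month outcome.
- **Weekly checks.** Under Assessment and procedures, an assistant reviews "the dropout rate, and correct respect of application of enrolment criteria". This reduces arbitrary removal but does not secure follow-up.
- **Timing.** Analysis was planned from May 2014 after a 12-month follow-up, so most treatment courses were probably over at publication in April 2014. New wording alone would then change little, and the gain lies in recovering patients already removed.

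**Conclusion.** The concern holds. Followed literally, the two sections take randomised patients out of the primary comparison for reasons that can be related to sick leave, in a trial whose practitioners know the arm. Under the stated assumptions the shift is about 0.5 to 4.4 days against a 30-day target. It is probably modest, and its direction cannot be predicted. The size rests on an SD implied by the sample-size statement, an assumed excess of 0.5 to 1.5 SD among those removed, assumed gaps in removal, and outcomes not being obtained after removal. It should be fixed because the bias is avoidable with a data source that the trial already uses.

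**What to change.** Reword Withdrawal criteria and align Concomitant treatments:

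- A new non-inclusion criterion, a prohibited treatment or an investigator's decision may stop the allocated programme only. Stopping treatment remains a clinical decision.
- Only the patient's withdrawal of consent ends data collection.
- All other randomised patients stay in follow-up and are analysed in their randomised arm. Their 12-month sick leave is obtained through the insurer check, and SF-36 and DPQ are sought at 6 and 12 months.
- Record the date, reason and arm of each stop, and state which triggers the 5-week limit covers.
- Because data collection was ongoing (Trial status), recover 12-month sick leave where possible for patients already removed who did not withdraw consent.

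**Cost.** Small: two paragraphs of wording, a few follow-up contacts and some insurer queries. Queries about patients already told that they are out of the study may need ethics or data-protection clearance. Some of these patients may not be recoverable, and questionnaires missed at 6 months are lost. Keeping patients who stopped their programme or had a prohibited treatment dilutes the contrast slightly, as intention to treat accepts.
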